### Discontinuation/withdrawal of participants and ‘stopping rules’

Participants will be withdrawn from the treatment prior to 8 weeks should there be over 50% increase in seizure frequency from baseline or if side effects, such as diarrhoea or constipation, are not resolved by dietary manipulation or medication. Withdrawn patients will not be replaced, but will have scheduled follow-up assessments.

### Deliverability and feasibility

An initial pilot study involving two centres over 12 months will aim to recruit approximately 20% of the total sample required: 35 participants over 12 months.

The pilot study will run in two centres in London: Great Ormond Street Hospital for Children and Evelina London Children’s Hospital over the initial 12 months. We will aim to assess approximately 50 eligible patients in this time frame. Additionally, adverse events (AEs) will be monitored and data on safety will be reviewed. We will progress to the full study if the following are achieved:Achieving a 60% recruitment rate; 30 families agreeing to randomisationNo more than 10 (29%) failing to complete the 8-week trial period

The main study will proceed to include recruitment from the further seven centres should the above criteria be met. Recruitment will be expected at a rate of 28/year from GOSH, and approximately 7/year from the remaining seven centres (total 84/year). This enables a completed primary outcome in the desired 160 children.

### Outcomes

The primary outcome will be the number of seizures experienced during weeks 6–8 compared to the number of seizures in the baseline period.

Secondary outcomes will include (at 8 weeks):Number of children seizure freeResponder rate, defined as the number showing more than a 50% improvement in seizure frequency compared to baseline (taken as the mean daily seizure frequency over the observation baseline period immediately preceding the 8-week review)Tolerance to KD as assessed by side effect questionnaire and blood resultsRelationship between medium-chain fatty acids and seizure control

Secondary outcomes will also include (at 12 months):Retention on treatment (the number of participants who remain on the KD, or the prescribed AED, at 12 months)Quality of life (as measured by the Infant Toddler Quality of Life Questionnaire)Neurodevelopmental outcome (as measured by the Vineland Adaptive Behaviour Scales)

Plasma profiles of medium-chain fatty acids will be evaluated at baseline and at 8 weeks. Assessment of mitochondrial function (respiratory-chain enzymes) and enrichment (citrate synthase) will be determined in white cells and platelets. The effect of specific ratios of medium-chain fatty acids, to mimic patient plasma profiles, upon neuronal mitochondrial function/enrichment (biochemical plus electron microscopy studies) will be documented. Additionally, such fatty acid profiles will be studied, with regards to antiepileptic effect, in an established in vitro (hippocampal slice) model.

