**Methods/design:**

An open-label RCT where eligible children (age 3 months to 2 years with epilepsy who have failed two antiepileptic drugs (AEDs)) undergo baseline assessment, including medical and seizure history. Participants then start an observation period (7 or 14 days) with documentation of seizure frequency. Randomisation will occur on day 8 or day 15 to receive the KD or a further AED; the allocated treatment will commence on day 15, with instruction and training. A second assessment (4 weeks after start of treatment) will include a clinical review and tolerability questionnaire (modified Hague Scale of Side Effects – for those allocated to the KD group). Assessments will be repeated at 8 weeks after the start of treatment including biochemical investigations, after which, according to patient response, KD (diet group) or AED (standard AED group) will then be continued or changed. Those in the AED group who have failed to achieve seizure control at the 8-week assessment will then be offered KD outside the context of the trial. Those in the KD arm who fail to achieve seizure control will be changed to standard clinical management. All patients will be followed up for 12 months from randomisation for retention, seizure outcome, quality of life and neurodevelopmental status.

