## Methods/design

The project proposed is an open-label, randomised controlled, multicentre clinical trial of children aged 3 months to 2 years of age with epilepsy who have failed to respond to two or more pharmacological treatments (AED or corticosteroids), comparing KD to further AED treatment. The study will be conducted in two phases: first, we will carry out a pilot phase in two centres. If the pilot study recruits successfully, we will proceed to the full trial in a further seven centres. See Additional file 1 for a schematic of the trial design.

Eligible children will be consented via their parents. They will undergo baseline assessment including medical and seizure history, neurological and anthropometric examination, administration of quality of life (Infant and Toddler Quality of Life Questionnaire, [33]) and developmental (Vineland Adaptive Behaviour Questionnaire, [34]) questionnaires and biochemical investigations. They will then start a 2-week observation period with documentation of seizure frequency. If the child is prone to particularly frequent seizures in excess of two per day, then a minimum baseline period of 1 week would be considered sufficient. Food diaries required for diet calculation will be returned by post from all enrolled infants 1 week (or sooner for those with an unstable clinical condition) into the observation period. Standardised seizure records will be kept during the observation period and throughout the trial. Randomisation will be conducted using an Internet randomisation system provided by Sealed Envelope™ (Sealed Envelope Ltd.). Randomisation will occur on day 8 or day 15 for participants to receive the KD or a further AED; the allocated treatment will commence following randomisation, with instruction and training.

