### Statistical analysis

Analysis will be done by intention-to-treat. Baseline characteristics of participants in the control and intervention arms will be summarised. The primary outcome will be seizure count in the final 2 weeks of the intervention period and in the baseline assessment period. Data will be analysed using a Poisson mixed model to account for clustering by centre (synonymous with therapist). The randomised allocation will be entered into the model as a fixed effect as will an indicator of time point (baseline or end of study), whilst the centre will be included as a random effect. Analysis of secondary outcomes (those seizure free and responders) will be analysed using random-effects logistic models – centre being the random effects and randomised group a fixed effect. The process outcomes relating to tolerability and medium-chain fatty acids in the KD group will be analysed using random-effects modelling. Therapist effects will be investigated further in supportive analyses [7, 37].

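### The primary outcome is a raw seizure count although baseline may last 7 or 14 days, so an unchanged child with a 7-day baseline appears to double.

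*Protocol article*

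**What the plan says.** The protocol article states the primary outcome twice, both times as a count. The Outcomes section has "The primary outcome will be the number of seizures experienced during weeks 6–8 compared to the number of seizures in the baseline period". The Statistical analysis section has "The primary outcome will be seizure count in the final 2 weeks of the intervention period and in the baseline assessment period".

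The baseline period does not have one length. The Abstract says "Participants then start an observation period (7 or 14 days) with documentation of seizure frequency". The Methods/design section gives the standard case as "They will then start a 2-week observation period with documentation of seizure frequency" and adds that, for children with more than two seizures a day, "a minimum baseline period of 1 week would be considered sufficient". Randomisation is accordingly on day 8 or day 15.

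The analysis is described as follows: "Data will be analysed using a Poisson mixed model to account for clustering by centre (synonymous with therapist". Its terms are then listed: "The randomised allocation will be entered into the model as a fixed effect as will an indicator of time point (baseline or end of study", with centre as a random effect. Days observed do not appear.

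Two other parts of the article work on a frequency scale. The Sample size section uses percentage of baseline, where 100 stands for no change in seizure frequency. The responder definition under Outcomes refers to mean daily seizure frequency.

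**The concern.** A count can be compared with another count only if both cover the same length of time. Here the follow-up count covers 14 days for everyone, and the baseline count covers 14 days for some children and may cover 7 for others. For the second group the comparison mixes a change in seizure rate with a change in the length of the window.

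The children affected are not a random subset. The short baseline is allowed only for those with the most frequent seizures, and these children contribute most to a Poisson count model. The Abstract reports that an amendment shortened baseline for patients with a high seizure burden and that recruitment then increased, so the group may be sizeable. The article does not give its share.

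At stake are the meaning of the endpoint, the estimated change over time and the precision of the comparison between arms.

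**Working it through.** **1. The plan's own sample size reproduces.** Inputs from the Sample size section: 62% (SD 45) on the ketogenic diet (KD), 90% (SD 50) on a further antiepileptic drug (AED), 90% power, 5% significance (two-sided assumed).
- Pooled SD = √((45² + 50²)/2) = 47.57.
- n = 2 × (47.57 × (1.960 + 1.2816)/28)² = 60.6, so 61 per group.
- 10% dropout: 61/0.9 = 67.8, so 68.
- Inflation factor: 1 + (8 − 1) × 0.05 = 1.35, and 68 × 1.35 = 91.8, so 92 KD + 68 AED = 160.

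This calculation is on a scale where 100 means an unchanged frequency.

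**2. What the raw count gives.** For a child whose rate does not change, the count ratio is follow-up days divided by baseline days.
- 14-day baseline: 14/14 = 1.0 (100%).
- 7-day baseline: 14/7 = 2.0 (200%).

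Example: 3 seizures a day gives 3 × 7 = 21 at baseline and 3 × 14 = 42 at follow-up. With a true 50% reduction, follow-up is 21 and the child appears unchanged. The planned means of 62% and 90% would read as 124% and 180% in 7-day children.

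**3. Effect on the time term.** Let p be the share of children with a 7-day baseline (not in the article; assumed). With equal rates and no true change, the pooled ratio is 14/(14 − 7p).
- p = 0.25: 14/12.25 = 1.14.
- p = 0.50: 14/10.5 = 1.33.
- p = 0.50, with the 7-day children at five times the rate of the others (assumed): (0.5 × 5 × 14 + 0.5 × 14)/(0.5 × 5 × 7 + 0.5 × 14) = 42/24.5 = 1.71.

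**4. Effect on the comparison between arms.** With the same p in both arms, the factor cancels. At p = 0.5 and equal rates, KD reads 0.62 × 1.333 = 0.827 and AED reads 0.90 × 1.333 = 1.20. Their ratio is 0.689, the same as 0.62/0.90.

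With unequal shares it does not cancel. Under no treatment effect, 40% (KD) against 60% (AED) gives (14/11.2)/(14/9.8) = 0.875, and the reverse gives 1.14. For the size of chance imbalance at p = 0.5 with 92 and 68 children:
- SE of the difference in shares = √(0.25 × (1/92 + 1/68)) = 0.080.
- Slope of the log ratio in p = 1/(2 − p) = 0.667.
- 95% range = exp(±1.96 × 0.080 × 0.667), about 0.90 to 1.11.

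**5. Precision, as an illustration.** Suppose the analysis were a per-child log ratio. A mixture of 7- and 14-day baselines adds p(1 − p)(ln 2)² to each child's variance. Log variances implied by the planning values are ln(1 + (45/62)²) = 0.423 for KD and ln(1 + (50/90)²) = 0.269 for AED, sum 0.692.
- p = 0.50: added 0.120 per arm, 0.240 in total. Variance ratio (0.692 + 0.240)/0.692 = 1.35. Power = Φ(3.2416/√1.35 − 1.96), about 80%.
- p = 0.25: added 0.090 per arm, 0.180 in total. Variance ratio 1.26. Power about 82%.

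As a check on the untransformed percentage scale, each arm has mean m(1 + p) and second moment (m² + s²)(1 + 3p). With 61 per group this gives about 77% power at p = 0.25 and 78% at p = 0.50.

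**6. After the repair.** Divided by days observed, an unchanged child scores 1.00 whatever the baseline length. Step 1 is untouched.

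**The case against.** The strongest defence is that an exposure offset is the kind of detail a condensed article leaves to the statistical analysis plan, which is not shown, and that the article's intent is plainly about frequency. That is fair as far as it goes: the absence of an offset from the model description would not by itself be a finding. But the outcome is stated as a count in two places. An offset elsewhere would repair the analysis and still leave the protocol's endpoint saying something different.

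The article also permits, rather than requires, a 7-day baseline, and it does not say how many children have one. This stands. The doubling applies to each child who has one, but the overall impact cannot be fixed from the article.

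Three stronger readings are tempting and not supported.
- *The treatment comparison is biased.* A reader might infer this from a factor of two. Baseline length is decided before allocation, so its mix is balanced in expectation. What remains is chance imbalance, since the article describes simple randomisation.
- *The two sections specify contradictory follow-up windows.* Weeks 6–8 can be read as three weeks, which would make the ratios in step 2 of the working 3.0 and 1.5. The natural reading is from the end of week 6 to the end of week 8, the same 14 days as the final 2 weeks of an 8-week intervention. The Discussion supports this with its 4–6 weeks of titration followed by at least 2 weeks for seizure assessment. The wording is loose, not contradictory.
- *Children withdrawn early would be scored over a different period.* The Discontinuation section says "Participants will be withdrawn from the treatment prior to 8 weeks should there be over 50% increase in seizure frequency from baseline", and a reader might infer that such a child's intervention period ends there. The article does not say so. It specifies intention-to-treat analysis and continued scheduled follow-up for withdrawn children, which points to week-8 data for everyone.

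**Conclusion.** The point holds as a badly fixed definition of the primary endpoint. The doubling for an unchanged child with a 7-day baseline is arithmetic from the stated windows and rests on no assumption beyond taking the count wording as written. So does the conflict with the frequency scale of the sample size and the responder outcome.

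The consequences are for within-child change, the time effect, precision and exposure to chance imbalance, concentrated in the children with the highest seizure rates. No systematic error in the comparison between arms is shown.

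The fall from 90% to about 80–82% power is illustrative. It assumes 7-day shares of 25% to 50% and describes a per-child log-ratio analysis, not the planned Poisson mixed model. The imbalance range of 0.90 to 1.11 assumes a 50% share and equal rates.

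**What to change.** Define the primary outcome in both sections as seizures per day observed. Equivalently, keep counts and add the log of days with diary data as an offset in the Poisson model. State one follow-up window in days, the 14 days ending at week 8 after the start of treatment, for all randomised children, and use it in place of the weeks 6–8 wording.

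The cost is a change of wording and one model term. Standardised seizure records are already kept during the observation period and throughout the trial, so no new data are needed. The sample size stays at 160. The Trial status section reports 29 children randomised, so the change can be made well before analysis.

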The randomisation schedule will be independently generated and held by Sealed Envelope™. Allocations will be released by email to the coordinating centres once the investigator or research nurse has entered eligible participant information into the web-based randomisation service. Participants will be allocated to either the KD or further AED arm using a simple, concealed, randomisation method. Randomisation will aim to achieve 92 in the KD group versus 68 participants in the further AED arm (see calculation in ‘Sample size’ section). An Enrollment Log will be maintained to keep records of the screened and randomised patients at each site. Withdrawn patients will not be replaced and replacement numbers will not be issued. Whilst it will not be possible to blind participants to their treatment allocation, efforts will be made to minimise expectation bias by emphasising in the trial literature that the evidence supporting the KD for seizure control is currently limited.

A second assessment (4 weeks after start of treatment) will include clinical review and a tolerability questionnaire (modified Hague Scale of Side Effects – see Additional file 2). Assessments will be repeated at 8 weeks after the start of treatment including clinical review, administration of the Infant and Toddler Quality of Life Questionnaire, the tolerability questionnaire, and biochemical investigations. After the 8-week assessment, according to patient’s clinical response to treatment with regards seizure outcome and tolerability, the KD (diet group) or AED (standard AED group) will then be continued or changed. Those in the AED group who have failed to achieve seizure control at the 8-week assessment will then be offered the KD outside the context of the trial. Those on the KD who have failed to achieve seizure improvement at the 8-week assessment will continue with medical management, as per clinician decision. All participants will be followed up for 12 months following randomisation for retention, seizure outcome and neurodevelopmental status. See Fig. 1 (Standard Protocol Items: Recommendations for Interventional Trials (SPIRIT) figure: schedule of enrollment, interventions and assessments) and Additional file 3 for the SPIRIT 2013 Checklist (recommended items to address in a clinical trial protocol and related documents).

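### The responder definition contradicts itself: its bracket merges the pre-randomisation baseline with the on-treatment window before the 8-week review

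*Protocol article*

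**What the plan says.** The responder rate stands in the Outcomes section of the protocol article, under the list that opens "Secondary outcomes will include (at 8 weeks"). A responder is a child with an improvement of more than 50% relative to baseline. A bracket follows: "taken as the mean daily seizure frequency over the observation baseline period immediately preceding the 8-week review".

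The timing of the periods it refers to is given elsewhere in the article.

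- **Observation period** (Methods/design): "They will then start a 2-week observation period with documentation of seizure frequency". One week is enough for children with more than two seizures a day.
- **Randomisation and treatment start** (Methods/design): "Randomisation will occur on day 8 or day 15 for participants to receive the KD or a further AED; the allocated treatment will commence following". The event that treatment follows is the randomisation itself.
- **8-week review** (Methods/design): "Assessments will be repeated at 8 weeks after the start of treatment including clinical review".
- **Primary outcome** (Outcomes): "The primary outcome will be the number of seizures experienced during weeks 6–8 compared to the number of seizures in the baseline period".
- **Primary analysis** (Statistical analysis): "The primary outcome will be seizure count in the final 2 weeks of the intervention period and in the baseline assessment period".
- **Analysis of responders** (Statistical analysis): "Analysis of secondary outcomes (those seizure free and responders) will be analysed using random-effects logistic models", with centre as a random effect and randomised group as a fixed effect. The responder windows are not restated there.

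**The concern.** A responder rate needs two windows for each child: a reference before treatment and a follow-up on treatment. The bracket supplies one window and gives it features of both. Its noun phrase names the observation baseline; its timing clause puts that period at the end of treatment. Both cannot be true of the same days.

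Two things are at stake. The stated comparator cannot be applied as written. And because the only window described is this merged one, the length and placing of the follow-up window are left open beyond the general 8-week time point. For an outcome that dichotomises at 50%, the choice of window can change how a child is classified, and in an open-label trial that choice should be fixed in the text.

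**Working it through.** **The plan's own figures.** The article gives no expected responder rate, so there is no figure to reproduce for this outcome. The sample size rests on mean percentages of baseline seizures and reproduces without the responder rule (two-sided 5% assumed):

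- Difference 90 − 62 = 28; mean variance (45² + 50²)/2 = 2262.5.
- n per group = 2 × (1.960 + 1.282)² × 2262.5 / 28² = 60.7, rounded up to 61.
- 61/0.9 = 67.8, so 68. Inflation 1 + (8 − 1) × 0.05 = 1.35, and 68 × 1.35 = 91.8, so 92. Total 92 + 68 = 160.

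The responder definition enters none of these steps.

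**The windows on one timeline.** Day 1 is the start of the observation period. Treatment is taken to start on the day of randomisation; any delay only lengthens the gap.

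| Period | Randomised on day 8 | Randomised on day 15 |
|---|---|---|
| Observation period | days 1–7 | days 1–14 |
| Treatment starts | day 8 | day 15 |
| 8-week review (start + 56 days) | day 64 | day 71 |
| 14 days just before the review | days 50–63 | days 57–70 |

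From the end of the observation period to the start of the pre-review fortnight there are 42 full days on treatment (days 8–49 or 15–56). No day belongs to both periods, so an observation period that immediately precedes the 8-week review does not exist.

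**Possible readings of the bracket.**

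1. It defines baseline, and the timing clause is right. The reference is then on treatment, and the outcome does not measure response to treatment.
2. It defines baseline, and the timing clause is a slip. The reference is the pre-randomisation period, but no follow-up window is given.
3. It describes the 8-week frequency, and the word baseline is a slip. The reference is again pre-randomisation by inference. The follow-up window ends at the review, but its length is not given.

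**Effect on one child** (illustrative rates, not from the article). With 10 seizures a day before randomisation and 2 a day at the end of treatment, readings 2 and 3 give (10 − 2)/10 = 80%, a responder. Reading 1 with the same pre-review window on both sides gives (2 − 2)/2 = 0%. For a child who is seizure free at the end it gives 0/0.

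**Why the follow-up window still matters under readings 2 and 3** (again illustrative). The primary outcome does not settle the length: weeks 6 to 8 can be counted as two weeks or three, whereas Statistical analysis specifies two. Take 10 a day at baseline, 8 a day in week 6, and 4 a day in weeks 7 and 8.

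- Last 14 days: mean 4, improvement (10 − 4)/10 = 60%, a responder.
- Weeks 6, 7 and 8: mean (8 + 4 + 4)/3 = 5.33, improvement (10 − 5.33)/10 = 47%, a non-responder.

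**The case against.** The strongest reply is that the meaning can be recovered. The observation period is the article's own term for the phase before randomisation, and both statements of the primary outcome keep baseline apart from the end of treatment. A competent analyst would use the pre-randomisation rate as the reference. That stands, and it limits the point to a correction of wording in a secondary outcome. It does not remove the point: no other section states the responder comparator correctly, and recovering the baseline does not supply the follow-up window.

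A reader might infer more: that the rule compares treatment with itself, so that no child can respond and the rate is 0% in both arms. The documents do not support this. It keeps the timing clause, discards the words that name the observation baseline, and assumes a follow-up window that the definition does not state. It is also a calculation that no analyst would adopt.

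A reader might also infer that the secondary logistic models lose power because they name only group and centre. The article does not show how strongly baseline frequency predicts either outcome, and no power calculation supports the claim. Response is already expressed relative to each child's own baseline. Covariates for secondary models are commonly left to the analysis plan, which is not at hand. Adding one also changes which odds ratio is estimated. It is an option, not a correction of an error.

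**Conclusion.** The responder definition is wrong as written. It places the baseline immediately before the 8-week review, when every child has been on allocated treatment or in follow-up for eight weeks, and it leaves the follow-up window without a separate definition. This rests only on the article's own timing and on no outside figure.

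The reach is limited: one secondary outcome, probably a drafting slip, with an intended baseline that can be inferred. The primary outcome, its analysis and the total of 160 do not change. The worked rates show how one child's classification can turn on the window; they are not an estimate of bias in the trial's responder rate, and the documents give no basis for one.

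**What to change.** Replace the bracketed definition with one that names both windows. A responder is a child whose mean daily seizure frequency over the last two weeks of treatment before the 8-week review is reduced by more than 50% relative to the mean daily frequency over the 7- or 14-day observation period before randomisation. Keep daily rates, because the baseline differs in length between children. The two-week follow-up matches the window in Statistical analysis.

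The cost is one sentence. Seizure records are already kept through the observation period and the trial. The article reports 29 children randomised of the planned 160, so at that point the wording could be settled well before analysis.

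Optional: add log baseline daily seizure frequency as a covariate in the secondary logistic models, chiefly for seizure freedom, where baseline is not already part of the outcome. The variable is already collected. If it is added, it should be specified before the data are analysed, and no gain in power should be claimed without a calculation.
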